**Figure 1 F1:**
[figure not shown]
**Algorithm of the study**.

The stages of this study are the following:

Phase Recruitment and selection:

1 The recruitment of the PCT: The project is explained to professionals belonging to the Health Centre. Those interested in participating in the recruiting of patients will sign a commitment of participation in the Project. The participants will be recruited by these professionals and their inclusion will be consecutive. Once the recruitment has ended, the groups will be randomized in the intervention or control group. Persons interested will fill up an application form for the Workshop, which will be available in their Health Care Center (HCC) and where they have to give their name, phone number, and time availability.

The Blood Pressure (BP) and Weight data will be gathered (in those persons who consent), at an individual visit after the informative meeting. They will be asked to have a Lipid Profile (if it is not available in their clinical history in a 3 months period before the workshops begins), and again after 12 months.

Phase The Forming of the Study Groups

2 Based on the persons who have given their consent to participate, an random assignation to one or another group will take place, and the workshops will then start (with groups of 12 to 15 persons in each).

Phase Intervention (only in the group intervened)

3 The group intervention then starts in 8 sessions in which life activities will be approached in a progressive manner. During the sessions, tools will be offered to increase knowledge and develop abilities and motivations that help with life activities and the progressive incorporation of healthy habits. At the end of each session support material will be handed out with the session's contents and indications of activities to practice during the week.

The workshops will be offered at different schedules to facilitate assistance. The contents of the sessions are in Table 1.

**Table 1 T1:** Subject matter of the sessions in the work shop

Session	Content
1	Breathing. Tobacco, learning from experience.

2.	Eating and drinking adequately, a balanced diet.

3.	Elimination. The importance of regular disposal. Guides to avoid constipation. Hygiene. The importance of personal hygiene.

4.	Movement and maintaining adequate positions. Doing physical activity. Wearing adequate clothes.

5.	Sleep and rest. Recommendations for a good rest and sleep. Leisure activities. The importance of dedication time to leisure.

6.	Avoid physical and emotional dangers. Self-esteem.

7.	Communication with others and social interaction. Managing one's emotions.

8.	Work and feel useful. The importance of activities that produce a sense of satisfaction.

Each session starts with a breathing exercise that helps participants to center themselves in the group. Next they share the week's experiences and clarify doubts. Followed by the theoretical content about the subject of the session and the practical exercises that to be done during the next week. The session ends with a space to clarify doubts and share reflections that have come up through the exposure of the theoretical concepts.

At the end of each session we hand out texts to be kept in their files and that will form, at the end of the Health Workshop, a MANUAL OF HEALTH CARE AND MAINTENANCE.

We have elaborated specific material, (with slides and points dealt with in the sessions) to ensure the unification of the message given. Also, we have elaborated support and reminder material for each session which gathers all the contents of the sessions. Such material is handed out at the end of each session to be kept in the files provided at the beginning of the Health Workshop, and which will, in the end, form a Manual for Health Self-Care and Maintenance.

The control group will continue to receive normal attention and will have the possibility, if they so desire, of doing the Health Workshops at the end of the Project, (if it has proven effective), once the 12 months are over with the last evaluation.

Phase Closing of the Project

4 Gathering and analyzing the last data and communicating the results.

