**Methods/Design:**

Controlled and random clinical testing, comparing a group of persons who have participated in the Health Workshops with a control group of similar characteristics who have not participated in the Health Workshops.

Field of study: the research is being done in Health Centers of the city of Barcelona, Spain.

Population studied: The group is composed of 108 persons that are actually doing the Health Workshops, and 108 that are not and form the control group. They are assigned at random to one group or the other.

Data Analysis: With Student's t-distribution test to compare the differences between numerical variables or their non parametric equivalent if the variable does not comply with the criteria of normality. (Kolmogorov-Smirnof test). Chi-square test to compare the differences between categorical variables and the Logistic Regression Model to analyze different meaningful variables by dichotomous analysis related to the intervention.

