## Method/Design

Design: Cluster randomized trial, controlled and multicentric, comparing one group of patients that take part in the Health Workshops, with another group of similar characteristics that don't.

Setting: The study will be done in Heath Care Centers of Barcelona City.

Randomization unit: Primary care Teams (PCT)

Study Population: Population around the Centers that participate in the Study and that meet the criteria of inclusion.

Inclusion criteria:

• Persons of both sexes between 18 and 65 who consent to do so.

Exclusion criteria:

• If there is an objection to participating during a period of 12 months.

• If there a language difficulty, unable to understand or express in Spanish or Catalan.

• If there are acute mental problems.

• Other health problems which may be a difficulty in following the workshop, (like terminals, organic pathology...).

Sample size calculation: Accepting an Alfa risk of 0.05 and a Beta risk of 0.2 in a bilateral contrast, 108 individuals per group are needed in order to detect how statistically effective it is in a 20% difference between groups in quality of life with the SF-36 Questionnaire. We have estimated a 10% rate of loss in participation. The ARCOSENO approximation has been used.

Variables in the study: We collect socio-demographic variables from all participants: age, sex, studies, employment or work situation.

Principal Variable: HRQOL measured by means of SF-36 Questionnaire. We have selected the quality of life perceived indicator as the main variable as it is sensible to small changes [19].

Variables related to the intervention:

• Number of sessions the person has attended.

• IPAC Questionnaire for variables related to physical activity (the IPAC questionnaire has been used in research around this area so it allows us to compare the data obtained.)

• The variables related to eating habits will be collected by means of Questionnaire PREDIMED [15], which is validated and used in our area, as so allow us to compare results.

• Blood Pressure, Lipid Profile, Height, Weight, will be gathered from the computerized clinical history.

• To estimate the costs we will add the time spent by professionals directly related with the intervention (telephone calls, meetings with participants, gathering of data, workshops...)

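### The Methods name the primary care team as the randomisation unit, the abstract names the person, and the sample size and analyses fit only the person

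*Protocol article*

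**What the plan says.** The protocol article speaks to the unit of randomisation in four places.

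- **Method/Design, design and unit lines:** "Design: Cluster randomized trial, controlled and multicentric", and then "Randomization unit: Primary care Teams (PCT").
- **Abstract, Methods/Design:** the trial is called controlled and random, without the word cluster. Directly after the 108 workshop and 108 control persons it says: "They are assigned at random to one group or the other".
- **Description of the Study, stage 1 (recruitment and selection):** "Once the recruitment has ended, the groups will be randomized in the intervention or control group". What the groups are is not said.
- **Description of the Study, stage 2 (forming of the study groups):** "Based on the persons who have given their consent to participate, an random assignation to one or another group will take place". Workshops of 12 to 15 persons then start.

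The sample size paragraph in Method/Design counts persons: "Accepting an Alfa risk of 0.05 and a Beta risk of 0.2 in a bilateral contrast", "108 individuals per group are needed" to detect a "20% difference between groups in quality of life with the SF-36 Questionnaire". It adds a 10% loss and names the arcsine approximation.

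The abstract names t-tests, chi-square tests and logistic regression. The Data analysis section names paired t-tests, McNemar tests and multiple regression on the change in SF-36. Neither has a term for team.

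**The concern.** The unit of randomisation determines who is allocated, how many independent units the trial has, which analysis is valid and how the design must be reported. Two units are stated here, and the choice cannot be repaired after allocation.

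The quantitative parts side with the person, while the design label sides with the team. If teams are allocated and persons are then analysed as independent, the standard errors are too small. The stated 5% error and 80% power would not hold.

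**Working it through.** **1. The statements side by side**

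| Place | Unit |
|---|---|
| Method/Design, design and unit lines | Primary care team, explicit |
| Abstract | Person, explicit: the subject of the sentence is the 108 + 108 persons |
| Stage 2 | Person on the natural reading; loosely worded |
| Stage 1 | Open: could be teams or groups of participants |
| Sample size | Individuals, no design effect mentioned |
| Analyses (abstract, Data analysis) | Individual-level, no term for team |

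The firm conflict is between Method/Design and the abstract. Stage 2 leans towards the abstract. Stage 1 does not decide the matter.

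**2. Reproducing 108 per group**

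Inputs from Method/Design: two-sided alpha 0.05, beta 0.2, a 20% difference, 10% loss, arcsine approximation. The two proportions are not given. I assume 0.40 and 0.60.

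- h = 2·asin(√0.60) − 2·asin(√0.40) = 0.403
- n = 2(1.960 + 0.842)² / h² = 96.8, so 97 per group
- 97 / 0.9 = 107.8, so 108 per group

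This is the published figure, and it needs no design effect. Other 20-point pairs, after loss, give 107 (0.45/0.65), 104 (0.50/0.70) and 90 (0.20/0.40 or 0.60/0.80).

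**3. The same 108 if teams are randomised**

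The article gives no team size, number of teams or ICC. I assume clusters of m = 12 to 15, borrowing the workshop size, and an ICC of 0.01 to 0.05.

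- Design effect: DE = 1 + (m − 1)·ICC
- Size needed: 97·DE rounded up, then divided by 0.9
- Power with 97 evaluable per group: Φ(h / √(2·DE/97) − 1.96)

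| m | ICC | DE | Needed per group | Power at 108 |
|---|---|---|---|---|
| 12 | 0.01 | 1.11 | 120 | 76% |
| 12 | 0.02 | 1.22 | 133 | 72% |
| 12 | 0.05 | 1.55 | 168 | 62% |
| 15 | 0.01 | 1.14 | 124 | 75% |
| 15 | 0.02 | 1.28 | 139 | 70% |
| 15 | 0.05 | 1.70 | 184 | 58% |

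With four teams of 27 per arm (108/4 = 27), DE is 1.26 at ICC 0.01 and 2.30 at ICC 0.05, and 137 to 249 per group would be needed. These normal approximations make no allowance for having few clusters, so they flatter the team design somewhat.

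**4. Type I error if teams are randomised and clustering is ignored**

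The true two-sided level is 2·Φ(−1.96/√DE). It is 6% at DE 1.11 and 13% at DE 1.70, against a nominal 5%.

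**The case against.** **Stage 1 and stage 2 can be read as team allocation.** Stage 1 sits under the recruitment of the teams, and randomising the groups after recruitment fits allocation of intact teams. Stage 2 bases the assignment on those who consented without saying that each person is allocated separately. This stands: the Description of the Study is ambiguous and cannot be counted as a firm second statement of person allocation. It does not rescue the abstract, whose unit is plainly the person.

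**An article condenses.** A missing clustering term alone could be left to a fuller analysis plan, and would be no finding. Here the article states the unit and states it two ways. It also gives a sample size with its formula and loss rate that fits only one of them.

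**The regression diagnostics include independence of residuals.** True, but the only remedy named is transformation of the dependent variable, which does not deal with clustering.

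**A design effect might be hidden in 108.** A pair such as 0.20/0.40 needs 90 per group, which leaves room for a factor of 108/90 = 1.2. This cannot be excluded arithmetically, but the article mentions no such factor.

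**Stronger readings that the article does not support.**

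- A reader might infer that centres would allocate differently from one another. Nothing gives centres charge of allocation; their professionals recruit.
- A reader might infer a calculable loss of power from contamination if persons in one centre are split. The handouts go into participants' own files and the research group delivers the workshops, so the amount of leakage is conjecture.
- A reader might take person allocation to give 216 independent observations. That ignores the 10% loss and possible correlation within workshop groups of 12 to 15.

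**Conclusion.** The point holds and should be fixed. Method/Design and the abstract state different randomisation units, the Description of the Study does not settle which applies, and the sample size and named analyses do not match the declared team unit.

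The size of the problem depends on which unit is true. If persons are randomised, it is one of labelling, and 108 per group stands given 0.40 against 0.60, apart from any within-workshop correlation. If teams are randomised, 108 per group gives roughly 76% down to 58% power, and a true error of about 6% to 13% if clustering is ignored. Those ranges rest on assumed proportions, cluster sizes and ICCs, so they illustrate the problem and do not estimate it for this trial.

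**What to change.** State one randomisation unit and use it in the abstract, in Method/Design and in both stages of the Description of the Study. If allocation has already taken place (the abstract writes in the present tense), the unit to state is the one actually used.

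- **If teams are the unit, as Method/Design declares:** say that every consenting person takes the arm of their team. Analyse with a term for team (a mixed model, or GEE, with a small-sample correction). Restate the power of 108 per group with a design effect, giving the assumed team size and ICC.
- **If persons are the unit:** delete the cluster label and the primary care team unit. Keep 108 per group, state the proportions behind it, and note that outcomes may correlate within workshop groups.

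Correcting the wording costs nothing. Team allocation costs a less favourable power figure and slightly more analysis work. Holding 80% power would take more persons, about 120 to 184 per group under the assumptions above.

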### Data analysis

The analysis will be done on an intention to treat basis. Those who have done less than six sessions will be considered withdrawals.

The descriptive analysis will be done in proportion to the quality variables and the average values for the quantities, with the corresponding measures of dispersion.

To observe the effect of the intervention in quality of life related to health, the change of habits and the costs derived from related resources, the T-Tests will be used for paired data and the McNemar Test or equivalents for quantitative or qualitative variables or their non parametric equivalents, if the distribution of the variable does not comply with the criteria of normality (Kolmogorov-Smirnof).

To analyze the factors that have influence over the changes of quality of life related to health (CVRS) and those related with the intervention, models of multiple regressions will be used. In each regression model the dependent variable will be derived from the calculation or the difference between ratings in the beginning of the study and the ratings at the end of the SF-36; the rest of the variables determined in the study will be included as independent variables. As the first step in the analysis of regression the adequate diagnosis will be done to detect extreme values and verify conditions of applicability (homocedastisity, normality and independence of waste). If needed the necessary transformations will be done in the dependent variables for the fulfillment of applicability conditions. The criteria of selection of variables for the estimation of multivariable models will be a Forward-Stepwise with the criteria of input of p < 0.05 and a criteria of output of p > 0.10.

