## Discussion

The Health Workshop proposed in the present study is a different approach to Health Promotion, placing the emphasis on self responsibly of the persons being cared for.

The weekly cadence of a session during 8 weeks with recommendations of activities and exercises for the week as well as group support is an opportunity to incorporate healthy habits and make a commitment to self-care.

The hand outs as a reminder and reference provide a Health Manual to consult once the Workshop is over.

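### The workshop runs in groups in one arm only: if outcomes correlate within those groups, the named independent-person tests understate standard errors and 108 per arm does not give the stated 80% power

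*Protocol article*

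**What the plan says.** The stage on forming the study groups (Protocol article, description of the study under Figure 1) says that after assignment "the workshops will then start (with groups of 12 to 15 persons in each". The next stage applies to the intervention arm alone. Controls have usual care for the 12 months. In every session participants share the week's experiences and their reflections, and the Discussion counts the group as part of how the workshop works: "group support is an opportunity to incorporate healthy habits".

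The abstract names the between-arm test: "With Student's t-distribution test to compare the differences between numerical variables", with chi-square tests and logistic regression for categorical data. The Data analysis section names paired t-tests and McNemar tests for the effect of the intervention. For factors that influence change in the SF-36, "models of multiple regressions will be used". Independence appears only as a residual check for those regressions, and the one remedy given is to transform the dependent variable.

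The sample-size paragraph of Method/Design reads "Accepting an Alfa risk of 0.05 and a Beta risk of 0.2 in a bilateral contrast" and concludes that "108 individuals per group are needed", for a 20% difference, a 10% loss and the arcsine approximation. It has no ICC or design effect.

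The unit of assignment is contradictory. The abstract and the group-forming stage read as assignment of persons; Method/Design names primary care teams as the randomisation unit.

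**The concern.** People who share a workshop for 8 weeks, and whose mutual support is meant to help them change habits, may have correlated outcomes. Controls form no such groups, so the correlation arises in one arm only (partial nesting). Every named test takes persons as independent, so the variance between workshop groups is left out of the standard error of the between-arm SF-36 difference. Intervals are then too narrow, and a few unusually cohesive groups could pass for an average effect of the workshop. Transforming the outcome does not remove correlation within groups.

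If persons are assigned, a term for the care team would not capture this, because the grouping arises after assignment.

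**Working it through.** **Inputs from the protocol.** Two-sided alpha 0.05; beta 0.2; a 20-point difference; 10% loss; 108 per arm; workshop groups of 12 to 15 in one arm.

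**Assumed, because not stated.** ICC 0.01 to 0.10. Base rates of 40% against 60%, chosen because they reproduce 108. The arcsine effect is also used as a standardised mean difference, since the protocol gives no SF-36 standard deviation.

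**1. The plan's own figure.** h = 2·asin(√0.6) − 2·asin(√0.4) = 0.4027. n = 2(1.96 + 0.84)²/h² = 96.8, so 97 per arm; 97/0.9 = 107.8, so 108. The stated figure is reproduced as a calculation for independent persons. (Rates of 45% against 65% give 107, 50% against 70% give 104, 60% against 80% give 90.) Power with 97 per arm is Φ(0.4027/√(2/97) − 1.96) = 80.1%, so no margin is left for clustering.

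**2. Number of groups.** 108/15 = 7.2 and 108/12 = 9 at enrolment; 97/12 = 8.1 after loss. About 8.

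**3. Variance with groups in one arm.** The intervention-arm design effect is DE = 1 + (m − 1)·ICC; the control arm has 1.

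- Power allowing for groups: Φ(h/√((DE + 1)/97) − 1.96)
- Type I error of the test that ignores them: 2[1 − Φ(1.96·√(2/(1 + DE)))]

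At m = 12 and ICC 0.05: DE = 1 + 11 × 0.05 = 1.55. Power = Φ(0.4027/√(2.55/97) − 1.96) = Φ(0.52) = 70.0%. Type I error = 2[1 − Φ(1.96 × 0.886)] = 8.3%.

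| ICC | DE, m = 12 to 15 | Type I error, groups ignored | Power, groups allowed for |
|---|---|---|---|
| 0 | 1.00 | 5.0% | 80.1% |
| 0.01 | 1.11 to 1.14 | 5.6% to 5.8% | 78.0% to 77.4% |
| 0.02 | 1.22 to 1.28 | 6.3% to 6.6% | 75.9% to 74.8% |
| 0.05 | 1.55 to 1.70 | 8.3% to 9.2% | 70.0% to 67.5% |
| 0.10 | 2.10 to 2.40 | 11.5% to 13.3% | 61.5% to 57.6% |

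**4. Allowing for few groups.** The normal approximation ignores that only about 8 groups inform the group variance. Simulation with 40,000 trials per cell: 8 groups of 12 against 97 controls, total variance 1 in each arm, difference 0 or 0.4027. The group-mean test uses Satterthwaite degrees of freedom.

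| ICC | Type I: t-test / group-mean test | Rejection at 0.4027: t-test / group-mean test |
|---|---|---|
| 0 | 4.9% / 5.0% | 79.6% / 76.5% |
| 0.01 | 5.7% / 5.1% | 78.9% / 74.2% |
| 0.02 | 6.2% / 5.1% | 78.0% / 71.5% |
| 0.05 | 8.4% / 5.1% | 76.6% / 64.6% |
| 0.10 | 11.6% / 5.3% | 74.6% / 55.3% |

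Repeat simulations put the t-test's type I error at 5.5% to 5.7%, 8.1% to 8.4% and 11.6% to 11.8% at ICC 0.01, 0.05 and 0.10.

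**5. If nobody is lost.** With 108 analysed per arm and m = 12, the formula in step 3 gives 82.2% power at ICC 0.01, 80.2% at 0.02 and 74.6% at 0.05.

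**6. Paired tests.** Applied within the intervention arm, they carry the full DE: 2[1 − Φ(1.96/√DE)] = 11.5% to 13.3% at ICC 0.05 for m = 12 to 15. They do not compare the arms.

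**The case against.** A reader might infer that the p-values are certainly too small and that 80% power is certainly missed. The document does not support that. It gives no ICC. At 0.01 the power loss is 2 to 3 points by normal approximation, and with no loss to follow-up power would still be about 82%. The research group delivers standard material itself (Quality control section), which may lower the ICC, although it does not remove effects of shared membership.

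If persons are assigned at random, sorting them into groups by schedule does not by itself inflate the variance of the arm mean. Only correlation created by delivery counts. If the workshop affects nobody, the ordinary test keeps its level; the inflation concerns a zero average effect with effects that vary by group.

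A reader might also infer that the groups are closed, or that this always adds to clustering by care team. The protocol gives only the group size and says that schedules vary. If teams are randomised and each workshop stays within one team, a team-level analysis already takes in workshop variance. Nothing says that workshops mix centres. A model with workshop groups but no team term would itself be invalid under team randomisation.

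Part of the simulated power loss is the price of the group-mean test: at ICC 0 it has 76.5% against 79.6%. The 65% at ICC 0.05 is therefore no fixed property of the trial; the normal approximation gives 70%. The between-arm t-test is named only in the abstract.

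These points limit the size and shape the fix. They leave the structure as it is: grouping in one arm, tests and a sample size for independent persons, and no margin at the planned loss.

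**Conclusion.** The point holds conditionally. If outcomes correlate within workshop groups, between-arm standard errors from the named tests are too small. Because 97 analysed per arm gives 80.1% under independence, any positive ICC then takes power below 80% at the planned loss.

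Over an assumed ICC of 0.01 to 0.10, with groups of 12 and the inferred 40% against 60%, the type I error of the unadjusted test is about 5.5% to 12%. Power is about 78% to 61% by normal approximation and 74% to 55% with few-group degrees of freedom. Under assignment of persons, the type I figure presupposes effects that vary by group. Under team randomisation, these figures leave out clustering by team, which would lower power further.

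**What to change.** 1. Reconcile the unit of assignment: persons (abstract and group-forming stage) or primary care teams (Method/Design).
2. Record the workshop group for which each intervention participant was scheduled, whether or not they attended.
3. If persons are assigned, analyse between-arm outcomes with a partially nested model: a random workshop-group effect in the intervention arm only, residual variance by arm, and Satterthwaite or Kenward-Roger degrees of freedom. Use the matching mixed logistic model for binary outcomes.
4. If teams are assigned, include a random team effect in both arms, and add the workshop-group effect where workshops are not identical to teams.
5. Replace the unqualified statement of "a Beta risk of 0.2" with the power at 108 per arm over a stated ICC range, and note that team randomisation would lower it further.

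The cost is analysis wording and one identifier known from scheduling. No extra participants are needed. The downside is wider intervals and a less favourable stated power, with only about 8 groups to estimate the workshop-group variance.
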